### Study blinding

2.6

Only 1 external research collaborator, with dental training, who will be responsible for the treatments (which will open the envelopes of randomization), will know which photobiomodulation treatment will be assigned to each patient. The identification of each group will be revealed by this collaborator to all involved only after statistical analysis of the data. Therefore, the researcher responsible for data collection and the statistician will be blinded to the treatments assigned to the groups. The patient will also be blind to the type of treatment performed, since the mini-implant placement treatment will be identical in both groups and the laser treatment for photobiomodulation will be simulated in the control group.

### Pretreatment evaluations

2.7

The patients will sign the Informed Consent Form Supplemental Digital Content (ANNEX 1) and the anamnesis Supplemental Digital Content (ANNEX 2) and the OHIP-14 questionnaire Supplemental Digital Content (ANNEX 3) will be applied. A form will be given to the patient to note the time and amount of medication taken. These data will be collected by 1 trained researcher (according to item.2.2 ’Researcher calibration’). Crevicular gingival fluid (CGF) will also be collected by this same professional. And also, the assessment of the impact of oral health on quality of life (OHIP-14). The visual analog scale will be applied immediately before the start of the procedure and will be asked about the amount of painkillers in the last week prior to the surgical procedure. Then the treatment will be performed as randomized by the researcher with dental training, specialist in orthodontics, responsible for the treatment.

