### Inclusion/exclusion criteria

2.4

Patients who are latex allergic, pregnant or breastfeeding, smokers, diabetics, patients undergoing head and neck radiotherapy, coagulation disorders requiring antibiotic prophylaxis for placement of mini-implants, with absolute indication for use of local anesthetics with vasoconstrictors, with decompensate systemic disease, with systemic or local infection (periodontitis or periodontal abscess), who have used anti-inflammatory drugs in the last 3 months before orthodontic treatment, will be excluded from the search.

Healthy patients (ASA I - negative medical history), systolic blood pressure less than 140 mm Hg and diastolic blood pressure less than 90 mm Hg, heart rate with 70 ± 20 beats/minute, requiring oral rehabilitation after loss of some posterior lower dental element (1st molar), with favorable periodontal condition to the installation of mini-implants and who agree and sign the informed consent, will be included.

Patients who may have any complications during the research period, such as: allergic reactions to any of the materials used, allergic reaction to paracetamol, have taken any other drug than the one available, etc. Or those who are in any way unable to attend any of the appointments on the scheduled dates (in all, will be 10 dates, within 3 months), change cities, or simply no longer wish to participate in the survey, will be automatically excluded, without any compromise or damage to it (with removal of the installed apparatus). They will still be advised not to go to other professionals to intervene or continue treatment. Patients will be assisted by researchers for all research problems.

Any questions during the research period should be informed to the researcher so that the researcher can take the appropriate measures (the latter should provide some form of personal contact).

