### Experimental design

2.10

Immediately before photobiomodulation (PBM) the responsible researcher will remove and open 1 envelope (without changing the numerical sequence of the other envelopes) and perform the indicated procedure. Thus, the 34 patients will be allocated to the experimental and control groups (considering a 20% drop out) as follows:

G1- Control group (n = 17) - Molar verticalization + laser simulation (placebo) - the treatment of molar verticalization adjacent to tooth loss will be performed with the use of mini-implants for skeletal anchorage (described in detail in the item “2.11 - Orthodontic verticalization mechanic and placement of the mini-implant”), followed by simulation of laser use, since it will be off, being applied at the same points and in the same period of the group that will be irradiated. To mimic the laser action the noise of the BIP will be recorded. Laser mimicking will occur immediately, 3 and 7 days after placement of the mini-implant, and the same sequence will be applied 30 and 60 days after force application (elastomeric ligature replacement), 5 points for buccal and 5 points for lingual. The analgesic pack will be delivered to the patient who will be advised to use only in case of pain. Visual analog scale (VAS), initial molar inclination (panoramic radiography), number of analgesics in the last 10 days, quality of life questionnaire (OHIP-14) and CGF collection will be assessed at baseline. Pain and use of rescue medication will be evaluated in all sessions. CGF collection will always be performed on the second day of laser application in the 3 months of research (totaling 3 collections, outside the baseline) and the questionnaire (OHIP) after 90 days. Another panoramic radiograph will be solicited before the removal of mini-implant (after 90 days).

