### Study variables

2.13

The primary variable of the study will be

Radiographic measurements to assess movement rate through tooth angulation vs time at baseline and the final of the treatment.

The secondary variables of the study will be:

Oral health-related quality of life (HRQoL) will be assessed using the OHIP-14 baseline questionnaire applied at baseline and 90 days after treatment.Assess pain during orthodontic verticalization movement using the Visual Analog Scale (VAS) at baseline 30, 60, and 90 days after mini-implant placementAssess the amount of painkillers ingested in the period to verify that this therapy is effective in reducing pain during baseline orthodontic movement, 3 and 7 days, 30, 60, and 90 days after mini-implant placement.evaluation of IL-6, IL-1β, IL-8, TNF-α and IL-10 cytokines by baseline (T0), 3 (T1) and 7 days (T2), and then only in T1 (on 30 and 60 days).

*Movement rate* - With the aid of a ruler (Morelli, Sorocaba, SP, Brazil) and a protractor (transparent Waleu 10290001), an initial panoramic radiography will be compared to a final panoramic radiography (on day 90th) to ascertain the amount (in degrees) of verticalization. By draw a mandibular line (where 1 end would be the lower posterior part of the right goniaco angle region and the other its corresponding left side) and the long axis of the tooth,^[45]^ forming an angle (the larger, the larger the inclination of the tooth). These measurements will be recorded in degrees in each patient's chart for further analysis.

*Pain during movement* - Will be assessed by applying the visual analog scale (VAS) with a 100 mm line, with both ends closed. One end has the indication “0” and the other “100” which means “no pain” and “unbearable pain” respectively. Marking instructions will always be given to the patient by the same operator. Each patient will be instructed to mark with a vertical stroke the point that best corresponds to the pain intensity at the moment of evaluation.^[46]^

*Rescue medication* - Another parameter analyzed will be the amount of analgesics ingested, as proposed by Bauer 2013.^[47]^ At the beginning of the research, a paracetamol (drug with purely analgesic effect^[48]^) card will be delivered to each patient. It should be stored until the end and its use will be released only in case of pain. At the end of the experiment, the number of pills will be evaluated as another parameter to measure pain. This data will be collected by an auxiliary.

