### Statistical analysis

2.14

Statistical analysis will be performed using only data obtained from patients who complete the study. The Kolmogorov-Smirnov test will be applied prior to data analysis to assess the normality of each parameter. Bidirectional analysis of variance (ANOVA) followed by Bonferroni test will be used to compare all measurements. All tests will be performed using Graphpad Prism 5 (GraphPad Software, San Diego, USA). The significance level will be set at p < 0.05.

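### The analgesic outcome has two baseline look-backs and differing follow-up counting schemes; if raw interval counts enter the two-way ANOVA, unequal windows create a false time effect and misplace any steady difference between arms

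*Protocol article*

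**What the plan says.** **Baseline.** Section 2.7 (Pretreatment evaluations) asks about "the amount of painkillers in the last week prior to the surgical procedure". Section 2.10 (Experimental design) lists, for both arms, "number of analgesics in the last 10 days".

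**Follow-up.** Three descriptions are given:
- Section 2.10, both arms: "Pain and use of rescue medication will be evaluated in all sessions". Section 2.4 puts the number of visits at ten ("in all, will be 10 dates, within 3 months").
- Section 2.13 (Study variables), list of secondary variables: the amount is assessed "during baseline orthodontic movement, 3 and 7 days, 30, 60, and 90 days after mini-implant placement".
- Section 2.13, Rescue medication paragraph: "At the end of the experiment, the number of pills will be evaluated as another parameter to measure pain".

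**Recording.** Section 2.7 provides a dated record: "A form will be given to the patient to note the time and amount of medication taken".

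**Analysis.** Section 2.14: "Bidirectional analysis of variance (ANOVA) followed by Bonferroni test will be used to compare all measurements". It does not say whether the analgesic variable is a count per interval, a daily rate or a 90-day total.

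**The concern.** The two baseline look-backs cannot both be followed. Baseline is more than a descriptor here, because section 2.13 names it as one of the time levels of this outcome. The follow-up descriptions yield about ten values, six values or one value per patient, and the single value has no time factor for a two-way ANOVA to use.

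The listed days are also unevenly spaced. A tablet count since the previous assessment grows with the length of the interval, so raw counts at different time levels measure different amounts of exposure. At stake is the reading of a secondary outcome that section 2.13 uses to judge whether the laser reduces pain. A time trend could come from the calendar alone. A steady benefit could seem to emerge late and to be absent at days 3 and 7, within the first laser cycle.

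**Working it through.** The documents give no expected tablet use, sample size or power for this outcome, so there is no figure of the plan to reproduce. The daily rates below are assumptions, shown as a range of 0.1 to 0.3 tablets/day.

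**Step 1: baseline look-back.** Expected count = daily rate × days. The ratio of the two versions is 10/7 = 1.43 at any constant rate. In absolute terms the gap is 3 days × 0.1 to 0.3 = 0.3 to 0.9 tablets.

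**Step 2: windows.** Successive differences of days 0, 3, 7, 30, 60, 90 are 3, 4, 23, 30 and 30 days (sum 90). Under the all-sessions scheme, the laser schedule in section 2.12 gives days 0, 3, 7, 30, 33, 37, 60, 63, 67 and 90. Those are ten dates, as section 2.4 says, with windows of 3, 4 and 23 days three times over. Both schemes are uneven.

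**Step 3: expected counts at a constant rate.**

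| Window | 0.1/day | 0.2/day | 0.3/day |
|---|---|---|---|
| Baseline, 7 days | 0.7 | 1.4 | 2.1 |
| Baseline, 10 days | 1.0 | 2.0 | 3.0 |
| Days 0–3 | 0.3 | 0.6 | 0.9 |
| Days 3–7 | 0.4 | 0.8 | 1.2 |
| Days 7–30 | 2.3 | 4.6 | 6.9 |
| Days 30–60 | 3.0 | 6.0 | 9.0 |
| Days 60–90 | 3.0 | 6.0 | 9.0 |

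Daily use never changes, yet the follow-up counts span a factor of 30/3 = 10.

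**Step 4: a constant difference between arms.** A difference of d tablets/day gives count differences of 3d, 4d, 23d, 30d and 30d, in total 90d. The first week holds 7/90 = 8% of it and the last three windows 83/90 = 92%. For 0.2 against 0.1 tablets/day the differences are 0.3, 0.4, 2.3, 3.0 and 3.0.

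**Step 5: simulation.** Poisson counts, 17 patients per arm, baseline (7 or 10 days) plus the five windows, two-way repeated-measures ANOVA at 0.05, 2,000 runs per setting. Rates were constant within the assumed range, either the same for all patients in an arm or gamma-distributed with a coefficient of variation (CV) of 1. The 2:1 ratio was applied at baseline as well, so that the true interaction in rates is exactly zero. A randomised trial would not be expected to show it there.

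| Rejection at 0.05 | Raw counts | Counts per day |
|---|---|---|
| Time, rate constant | 100% | 6–9% |
| Interaction, constant 2:1 rates, no spread between patients | 99–100% | 7–9% |
| Interaction, constant 2:1 rates, CV 1 | 55–59% | 7–9% |
| Interaction, equal rates, no spread | 7–8% | 7–8% |
| Interaction, equal rates, CV 1 | 10–11% | 7–8% |

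The group main effect on raw counts with equal rates was rejected in 4–5% of runs. That holds for the repeated-measures form. An ordinary two-way ANOVA that ignores the patient rejected it in 28–31% of runs on raw counts with CV 1, but also in 27–33% on per-day counts, so that inflation comes from ignoring the patient and not from the windows.

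**Step 6: does dividing by days cure it?** Only the mean. For Poisson counts at rate r, raw variances are 3r and 30r for the 3-day and 30-day windows. Per-day variances are r/3 and r/30. The tenfold imbalance is reversed, not removed.

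**The case against.** A reader might infer that the planned ANOVA manufactures a false treatment finding. The documents do not support that. Section 2.10 gives both arms the same windows and rules, so equal daily rates give equal expected counts in every window. Interaction error under equal rates rose only to 10–11%, and only with strong spread between patients. The large interaction needs a true rate difference; it misstates the timing of a real effect and does not invent one. This part of the objection stands.

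It is also fair that section 2.14 never says raw interval counts will be entered, and that an article may leave the derivation of a secondary variable to a fuller document. The follow-up schemes overlap as well: all sessions include the listed days, and the end count could simply be the final total. The dated form would let follow-up windows be rebuilt. Baseline use may be close to zero, since section 2.4 admits healthy patients and excludes recent users of anti-inflammatory drugs; the 1.43-fold gap would then be small in tablets.

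These points narrow the concern without removing it. The baseline look-backs contradict each other in the text, which is not omitted detail. Use before the study cannot be rebuilt, because the form is handed out only at pretreatment. The outcome is described only as an amount or a number of pills, with no daily rate mentioned, so counts are the natural reading.

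**Conclusion.** The concern holds in limited form. The 7-day and 10-day look-backs conflict and differ 1.43-fold in expected count at any constant rate. The counting schemes do not identify one analysed variable for the two-way ANOVA.

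Provided that counts since the previous listed day are analysed, a constant rate appears as a time effect, with a tenfold range of expected counts that follows from the window lengths alone. A steady difference between arms appears as an interaction, with 92% of it in the last three windows. The rejection percentages depend on the assumed rates and spread; the window ratios do not. There is no built-in between-arm effect when the arms do not differ, and in the repeated-measures form the group main effect is not distorted. The outcome is secondary and the primary angulation outcome is not affected. It should be corrected, but it does not threaten the trial's main conclusion.

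**What to change.** - **Sections 2.7 and 2.10:** state one baseline look-back, the same in both, before patients are asked. If some have already been asked, record which period each answer covers.
- **Sections 2.10 and 2.13:** state one set of counting times, taken from the dated form, and say how the end-of-study pill count relates to it.
- **Sections 2.13 and 2.14:** make total tablets over days 0 to 90 the main between-arm comparison and take it out of the two-way ANOVA. Section 2.14 analyses completers only, so every analysed patient has the same 90-day exposure.
- **By-window results, if wanted:** analyse them as rates, using a count model with log window length as offset and allowance for repeated measures within patient. ANOVA of raw counts has the window artefact, and ANOVA of per-day counts keeps the unequal variances.

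The cost is wording in four sections. No visit, form or measurement is added, because the form already records time and amount.

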### Anamnesis

2.8

Anamnesis will be performed in both groups. In addition to questions related to the patient's general health, demographic data (age, gender, marital status, occupation, educational level, living conditions, salary), medical history data (major complaint, current disease status, medical history, dental history, medications).

### Oral hygiene guidance (OHB)

2.9

All participants will receive oral hygiene guidance (OHB), Bass brushing technique, toothbrush specifications (soft bristles and small head), and dental floss (traditional Colgate)

### Experimental design

2.10

Immediately before photobiomodulation (PBM) the responsible researcher will remove and open 1 envelope (without changing the numerical sequence of the other envelopes) and perform the indicated procedure. Thus, the 34 patients will be allocated to the experimental and control groups (considering a 20% drop out) as follows:

G1- Control group (n = 17) - Molar verticalization + laser simulation (placebo) - the treatment of molar verticalization adjacent to tooth loss will be performed with the use of mini-implants for skeletal anchorage (described in detail in the item “2.11 - Orthodontic verticalization mechanic and placement of the mini-implant”), followed by simulation of laser use, since it will be off, being applied at the same points and in the same period of the group that will be irradiated. To mimic the laser action the noise of the BIP will be recorded. Laser mimicking will occur immediately, 3 and 7 days after placement of the mini-implant, and the same sequence will be applied 30 and 60 days after force application (elastomeric ligature replacement), 5 points for buccal and 5 points for lingual. The analgesic pack will be delivered to the patient who will be advised to use only in case of pain. Visual analog scale (VAS), initial molar inclination (panoramic radiography), number of analgesics in the last 10 days, quality of life questionnaire (OHIP-14) and CGF collection will be assessed at baseline. Pain and use of rescue medication will be evaluated in all sessions. CGF collection will always be performed on the second day of laser application in the 3 months of research (totaling 3 collections, outside the baseline) and the questionnaire (OHIP) after 90 days. Another panoramic radiograph will be solicited before the removal of mini-implant (after 90 days).

G2- Experimental group (n = 17) Molar verticalization + PBM (n = 17 + 3) - the treatment of molar verticalization adjacent to tooth loss will be performed with the use of mini-implants for skeletal anchorage (described in detail in the item “2.11 - Orthodontic verticalization mechanic and placement of the mini-implant”), followed by the use of laser. Immediately 3 and 7 days after surgery, the same sequence was applied 30 and 60 days after force application (elastomeric ligature change), 5 points for buccal and 5 points for lingual, following the long axis of the tooth. The analgesic pack will be delivered to the patient who will be advised to use only in case of pain. Visual analog scale, initial molar inclination (panoramic radiography), number of analgesics in the last 10 days, quality of life questionnaire (OHIP-14) and CGF collection will be assessed at baseline. Pain and the use of rescue medication will be evaluated in all sessions. CGF collection will always be performed on the second day of laser application in the 3 months of research (totaling 3 collections, outside the baseline) and the questionnaire OHIP-14 after 90 days. Another panoramic radiograph will be requested before the removal of mini-implant (after 90 days). (Fig. 1 )

### Orthodontic verticalization mechanic and placement of the mini-implant

2.11

At the first consultation, all patients will be clinically and radiographically evaluated, and a treatment plan will be drawn up. Given the need for molar verticalization, an orthodontic mini-implant (Morelli, Sorocaba, SP, Brazil) will be installed in the retromandibular region (Araújo, 2006). First there will be a local asepsis with 2% chlorhexidine solution (2% aqueous chlorhexidine - Rioquímica) and external asepsis with 0.2% chlorhexidine (0.2% aqueous chlorhexidine - Rioquímica). The site will be anesthetized with a carpule (quinelato), short gingival needle (Unoject - Nova DFL) and the anesthetic of choice will be Mepivacaine + 2% Epinephrine 1 ml (Mepiadre 2% 1: 100000 - Nova DFL). The anesthetic technique used will be the infiltrative (essentially local) at 3 points of the retromolar region (central, buccal and lingual). Once this is done, the region will be pre-drilled by about 4 mm with a spearhead coupled to a manual key (Morelli ). In order to have proper anchorage and primary stability, the dimensions of the mini-implant will be chosen based on panoramic radiography and the amount of cortical bone present in the region.^[42]^ Once the mini-implant has been selected (Morelli, Sorocaba, SP, Brazil), it will be locked into position using a kit-specific digital key (Morelli, Sorocaba, SP, Brazil). Being threaded clockwise until the intramucosal mini-implant is at the gingival level. A simple surgery, where there is no osseointegration of the mini-implant, being inserted only in the cortical bone, being therefore easy to remove, and can be activated (force application) immediately. After installation, a metallic orthodontic lingual button (Morelli, Sorocaba, SP, Brazil) will be glued to the molar mesial face to be verticalized. As the molar is verticalized, this lingual button may be retracted more distally so that the elastic always exerts the proper force (this will be evaluated at each patient return by the calibrated operator). For its installation, molar prophylaxis will be performed with a Robinson brush (Robinson straight CA - Microdont brush) and prophylactic paste (Herjos - Coltene), followed by water irrigation and drying. Once this is done, the dental surface will be conditioned with 37% phosphoric acid (Condac - FGM) for 45 seconds, followed by water irrigation for 15 seconds and subtle air drying from the triple syringe. Next, we have the application of single bond adhesive system (Adper Single Bond 2 - 3M Adhesive) and polymerization (Poly Wireless Curing - Kavo) for 5 seconds. The lingual button will be glued to the inclined molar mesial with orthodontic adhesive (Orthocem - FGM), and a small portion of it will be placed on the lingual button grid and, once it is in position, it will be light cured for 45 seconds. A gray chain elastomeric ligature (Morelli, Sorocaba, SP, Brazil) will attach the head of the mini-implant to the lingual button glued to the molar mesial. A light force of 150 g will be imposed (measured with a tensiometer - Morelli, Sorocaba, SP, Brazil)^[43,44]^ in all cases, regardless of tooth position. This chain elastic will be changed every 30 days for a period of 3 months. After 90 days of the experiment time, the mini-implants will be removed. This procedure involves local anesthesia with Mepivacaine + 2% Epinephrine 1 ml (Mepiadre 2% 1: 100000 - Nova DFL) and the mini-implant will be removed only with the digital key being turned counterclockwise. Since there is no osseointegration, its removal is simple and quick, requiring no incision or suture. Painkillers will be available if there is pain. Removal of the lingual button will be performed using bracket pliers (346R-Zatty Straight Bracket Orthodontic Pliers) and resin removal with high-speed diamond drill bits (FG – Fava flame diamond). After the trial period, for those patients who are interested will be offered the possibility to complete (if this 3 months of research has not been achieved) the full verticalization of this molar (ie the mini-implant and lingual button would not be removed after 90 days and changes of the elastic bandage would occur until the case was finalized), so that they could receive future oral rehabilitation (making it clear to the patient that they would no longer be part of the research, and that any charge resulting from this choice would not fit to the researcher).
